### Study population

The study population will include infants born at < 30 weeks’ gestation who never received infant formula, are admitted to one of the 29 participating tertiary NICUs in China, have parents who consent to the study, and have mothers who are willing to provide at least two feeds of fresh milk daily, 7 days a week until the infant is 32 weeks’ corrected age. Infants with major congenital anomalies or receiving palliative care, infants with mothers who are too ill to provide fresh human milk in the first week postpartum or are unable to provide at least two feeds of fresh milk a day, infants with congenital *Cytomegalic virus* (CMV) infection, and infants whose mothers have blood CMV-IgM (+) or CMV-DNA (+) or are unwilling to consent will be excluded. Congenital CMV-infection is defined as positive CMV NAT (or positive viral culture obtained from clinician-ordered testing) in blood or urine within 2 weeks of life [20].

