### Sample size

The sample size justification was based on the primary outcome and the hypothesis. A recent quality improvement study found that the incidence of the composite outcome mortality or NEC ≥ stage 2 was 29% in 25 Chinese NICUs [[name], written communication, October 2018]. Assuming a primary outcome rate of 29% for the control group, we estimated that a sample size of 3098 (1549 patients per arm) will achieve an 80% power to detect at least a 16% relative reduction in the incidence of the primary outcome in the fresh milk group when compared to the control group. With an average of 2397 eligible infants admitted to participating hospitals each year and an estimated enrollment rate of 60%, we expect to recruit 1438 infants per year and the study to take 2 years. We used the chi-square test for the power analysis, assuming a significant level of 0.05. Therefore, the proposed enrollment of 3098 patients will have sufficient power to test our hypothesis taking into account a possible 5% data loss to follow-up.

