### Statistical analysis

Data from the study will be analyzed on an intention-to-treat basis. Patient characteristics at baseline will be summarized within each of the groups using the descriptive statistical methods suggested by the CONSORT statement for randomized clinical trials. To examine the difference in the rate of the primary outcome between the control and fresh human milk groups, we will use the chi-square test. We will compare the secondary outcomes of the control and fresh milk groups using the chi-square test or Fisher exact test, as appropriate, for categorical variables and the Student T test or Wilcoxon Rank Sum test, as appropriate, for continuous variables.

As secondary analyses, we will also, if applicable, determine whether a variation exists in the treatment effect across the centers/NICUs by presenting the effects by individual centers/NICUs graphically. If variation is observed, we will further compare the binary outcomes using the Cochran-Mantel-Haenszel test to account for the effect of center, as well as conducting fixed-effect logistic regression (for binary outcomes) or linear regression (for continuous outcomes) without including treatment-center interaction term. The fixed-effect model including treatment-center interaction term will be further applied to examine the heterogeneity of the effect across centers when the variation in the center-effect is identified. If variation exist in the center-effect but no heterogeneity of the effect is observed, a marginal logistic or linear regression model with generalized estimating equations (GEE) approach will be applied to estimate the main treatment effect to account for the center effect. If the heterogeneity of the effect is observed, subgroup analysis stratified by the homogeneous centers using marginal models with GEE approach will be applied if applicable.

To examine whether a variation exists in the treatment effect across gestational age group (i.e., GA < 28 vs GA: 28–30), birth weight group (i.e., BW < 1000 g vs BW: 1000-1500 g) or upon receipt of probiotics, fixed-effect logistic or linear models will be used that include GA (or BW or probiotic) group and the interaction between treatment and GA group (or BW or probiotic), if applicable.

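### The secondary centre-adjusted analyses depend on variation seen in a graph of NICU effects, which chance alone will nearly always show, and an interaction step then selects the form of the estimate

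*Protocol article*

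**What the plan says.** All of this is in the Protocol article, Statistical analysis. The primary comparison is a plain chi-square test on all infants, with no condition attached. A chain of secondary analyses follows, each to be done where applicable:

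1. The plan will "determine whether a variation exists in the treatment effect across the centers/NICUs by presenting the effects by individual centers/NICUs graphically".
2. "If variation is observed, we will further compare the binary outcomes using the Cochran-Mantel-Haenszel test to account for the effect of center". Fixed-effect logistic or linear regression without an interaction term accompanies it.
3. "The fixed-effect model including treatment-center interaction term will be further applied to examine the heterogeneity of the effect across centers". This step is conditional on variation in what the text now calls the centre effect.
4. If no heterogeneity is found, a GEE model gives one main effect. If heterogeneity is found, GEE models are fitted within groups of centres regarded as homogeneous.

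The section Randomization and blinding says that allocation is blocked and stratified by NICU.

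**The concern.** There are three linked problems in what the chain fixes.

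- **The gate is visual.** Whether a centre-adjusted result is produced depends on how 29 small-sample effects look once outcomes are known.
- **Two ideas are mixed.** Step 1 concerns variation in the treatment effect. The Cochran-Mantel-Haenszel test and the no-interaction regression in step 2 target one common effect and allow only for differences in baseline risk between centres. Step 3 then speaks of the centre effect. A plot of treatment effects does not show baseline risk.
- **A pre-test selects the estimate.** The interaction result decides whether the secondary estimate is one GEE effect or several subgroup effects. Homogeneous groups of centres can be formed only from the observed outcomes.

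At stake is the secondary, centre-adjusted estimate. Its existence and form would depend on the data, although NICU-stratified randomization is reason enough to adjust for NICU in every case.

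**Working it through.** **Inputs from the Protocol article.** Study population: infants who "are admitted to one of the 29 participating tertiary NICUs in China". Sample size: "we estimated that a sample size of 3098 (1549 patients per arm) will achieve an 80% power"; "Assuming a primary outcome rate of 29% for the control group"; "to detect at least a 16% relative reduction in the incidence of the primary outcome in the fresh milk group"; "We used the chi-square test for the power analysis, assuming a significant level of 0.05". Statistical analysis: two-sided 0.05. The 5% loss is also from Sample size.

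**The plan's own figure.** The fresh-milk rate is 0.29 × 0.84 = 0.2436, a difference of 0.0464. The two-proportion formula at 80% power gives 1426 per arm, or 1468 with continuity correction. Allowing for 5% loss, 1468 / 0.95 gives 1546 per arm against 1549 stated. The inputs are therefore read correctly.

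**Infants per centre.** 3098 / 29 / 2 = 53.4 per arm per NICU, assuming equal centres.

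**What the graph would show under an equal effect.**
- SE of one centre's risk difference = √(0.29×0.71/53.4 + 0.2436×0.7564/53.4) = 0.0855. This is 8.5 points, 1.8 times the planned 4.64.
- With 53 per arm, the exact binomial probability that the fresh-milk rate exceeds the control rate in one centre is 0.257. The expected number is 29 × 0.257 = 7.5 NICUs.
- Simulation agrees: mean 7.5, 95% range 3 to 12, and a mean spread of about 35 points between best and worst centre.
- The probability that at least one NICU is reversed is 1 − (1 − 0.257)^29, above 0.999.
- With real heterogeneity (SD of the log odds ratio 0.25), the simulated mean is about 8 reversed NICUs. The count barely moves, so the graph does not discriminate.

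**Power of the interaction step.** The planned odds ratio is (0.2436/0.7564)/(0.29/0.71) = 0.788, log −0.238. The per-centre variance of the log odds ratio is v = 1/(53.4×0.29×0.71) + 1/(53.4×0.2436×0.7564) = 0.1925, so the SE is 0.439. The interaction has 29 − 1 = 28 df, and the 5% critical value is 41.34. For a between-centre SD τ, approximate power = P(χ²₂₈ > 41.34/(1 + τ²/v)). The documents give no τ, so the range is shown:

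| τ (assumed) | Power |
|---|---|
| 0.10 | 8% |
| 0.20 | 19% |
| 0.24 (about the whole planned log odds ratio) | 28% |
| 0.30 | 46% |
| 0.40 | 75% |
| 0.50 | 93% |

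Power of 80% needs τ of about 0.42. At τ = 0.238 the central 95% of true centre odds ratios runs from exp(−0.238 − 1.96×0.238) = 0.49 to exp(−0.238 + 1.96×0.238) = 1.26. Simulated likelihood-ratio tests, with equal and unequal centres, gave 21–24% at 0.20, 46–49% at 0.30 and 74–76% at 0.40. Their rejection rate with no heterogeneity was 6–8%. With 5% loss, power at τ = 0.238 is 26%. With 30 centres, which is how many the hospital list appears to name, it is 27%.

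**The case against.** The strongest defence is that nothing confirmatory rests on this chain. The primary chi-square is unconditional, and the sequence is labelled secondary and to be used where applicable. That stands. A reader might infer that the interaction test decides whether one effect may be claimed for all NICUs, or that a non-significant result will be taken as proof of equal effects. The plan says neither; the test only selects between two secondary presentations.

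A reader might also call the sequence backwards, with common-effect methods used just when the effect varies. That follows only if variation means treatment-effect variation throughout. The later wording about the centre effect suggests that differences in baseline risk may have been meant, for which the order of methods is ordinary. What stands is that the text begins with one concept and continues with the other.

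Nor is 28% power a property of the plan. It needs an assumed SD of about 0.24, and with large heterogeneity the test is adequate.

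If chance always shows variation, the adjusted analyses will in effect always be run, so step 1 does little harm. That is fair, but it argues for removing the condition. Numerical cut-offs might sit in an SAP that is not shown, and their absence is not the point. The article itself fixes a graph as the gate and outcome-based grouping as the remedy.

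Finally, a reader might infer that the interaction model cannot be fitted for the rarer outcomes. For NEC at the 6.2% given in Background, an empty centre-arm cell has probability 0.938^53.4 = 0.033, or about 1.9 of 58 cells. Those centres' estimates fail, but this does not show that the model as a whole is unusable.

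**Conclusion.** The point holds as a defect in the secondary analyses. The graphical gate is close to uninformative: about 7 to 8 of 29 NICUs would appear reversed under a perfectly equal effect, assuming equal centres and the design rates. The wording mixes treatment-effect variation with baseline-risk variation, and only the latter is addressed by the methods triggered. The interaction step is weak for moderate heterogeneity and adequate only when heterogeneity is large (8% to 93% power for an assumed SD of 0.10 to 0.50). It nevertheless selects the estimate and can lead to subgroups defined by their own results. The primary result and its sample size are not affected.

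**What to change.** - Delete the condition that variation be observed. Run the NICU-adjusted analysis (Cochran-Mantel-Haenszel, or regression adjusted for NICU) unconditionally for the primary outcome and, where event counts allow, for the secondary outcomes.
- Delete the routing by interaction result and the subgroups of homogeneous centres.
- For the primary composite only, report heterogeneity of the treatment effect across NICUs as an estimate with its interval, for example the SD of a random treatment-by-centre effect. State that it is descriptive and does not select which overall estimate is reported. The centre plot can stay as a display.

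Deleting the whole paragraph would be a mistake, because it would also remove the centre adjustment that NICU-stratified randomization calls for. The cost is analysis wording only. The small downside is that the heterogeneity interval will be wide with 29 centres.

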### Outcomes measures

The primary outcome of the study will be a composite of mortality or NEC ≥ stage 2. The secondary outcomes of the study will be mortality before discharge; NEC ≥ stage 2; NEC needing surgery; late-onset sepsis; retinopathy of prematurity (ROP) requiring treatment; bronchopulmonary dysplasia (BPD); change in weight, length, and head circumference; change in weight, length, and head circumference z-scores; time to full enteral feeds (160 mL/kg/day); and number and type of critical incident reports, including feeding errors. NEC will be defined according to Bell’s classification [24]. Sepsis will be defined as isolation of bacterial, fungal or viral organism from blood or cerebrospinal fluid in a symptomatic infant. ROP will be defined according to the International Committee for the Classification of Retinopathy of Prematurity [25]. BPD will be defined as oxygen need at 36 weeks’ postmenstrual age [26]. Weight, weight z-score, length and head circumference will be assessed on a weekly basis until the infant is 9 weeks (63 days) of age.

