In China, approximately 17% of infants born preterm die at home following discharge against medical advice [[name], written communication, October 2018]. Since we are using intention-to-treat analysis in our study, these infants will be included in our analysis. However, we will perform a subgroup analysis that only includes infants who were actively treated, which includes 1991 infants per year on average [[name], written communication, October 2018]. The primary outcome rate is 17%, on average, for infants who are actively treated; therefore, we estimate that a total sample size of 2292 infants (1146 per arm) will achieve an 80% power to detect at least a 25% relative reduction in the incidence of the primary outcome in the fresh milk group when compared to the control group.

We will also apply linear or nonlinear mixed-effect models for the longitudinal secondary outcomes (weight or change in weight z-score over time) to compare the rate of the change in the outcomes between the two groups, adjusted for the infant- and NICU- level characteristics if applicable. For secondary outcomes, no adjustment for multiple comparisons will be conducted.

For the primary outcome, to minimize possible bias due to drop out or missing data, we will also, if applicable, conduct logistic regression adjusted for propensity score estimated based on the infant and NICU characteristics available. A two-sided *p* value of < 0.05 will be used to determine the statistically significant difference.

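### Length and head circumference share the weekly schedule of weight, but only weight is given the longitudinal mixed model

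*Protocol article*

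**What the plan says.** All statements are in the protocol article.

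- **Outcomes measures, outcomes.** The secondary outcomes include "change in weight, length, and head circumference; change in weight, length, and head circumference z-scores". The three measures have equal standing.
- **Outcomes measures, schedule.** "Weight, weight z-score, length and head circumference will be assessed on a weekly basis until the infant is 9 weeks (63 days) of age". All three measures follow the same weekly timetable.
- **Statistical analysis, default test.** Continuous secondary outcomes are compared by "the Student T test or Wilcoxon Rank Sum test, as appropriate, for continuous variables".
- **Statistical analysis, longitudinal model.** "We will also apply linear or nonlinear mixed-effect models for the longitudinal secondary outcomes (weight or change in weight z-score over time", with the stated aim "to compare the rate of the change in the outcomes between the two groups". The bracket lists weight or change in weight z-score and nothing else, and it is not marked as an example.

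The regression and GEE models elsewhere in the Statistical analysis section deal with centre effects and subgroups. They do not deal with repeated measurements on an infant.

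**The concern.** Measures collected on the same timetable are analysed differently, and no reason is given. The plan treats weight as longitudinal. Length and head circumference are equally longitudinal by its own schedule, yet they receive only the default two-group test on a change.

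Two things are at stake, both confined to secondary outcomes:

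1. **Unused measurements.** A change score takes a start and an end value. The weekly readings in between are collected but do not enter the comparison.
2. **Infants without the end value.** They have no change score. The article expects such infants: the Background gives 25% mortality in this population, and the Discussion allows for 10% of families dropping out. The missing-data adjustment in the Statistical analysis section is stated for the primary outcome only.

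**Working it through.** **The plan's own figure.** The article gives no figure for the growth outcomes. Its only comparable figure is the primary sample size of 1549 per arm. The inputs are 29% in controls, a 16% relative reduction (0.29 × 0.84 = 0.2436), two-sided 5%, 80% power and 5% loss. The two-proportion formula with continuity correction gives 1468 per arm, and 1468 / 0.95 rounds up to 1546, which agrees closely. Nothing below changes it.

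**Inputs for this point**
- Weekly values to day 63 (Outcomes measures): at most K = 10, weeks 0 to 9, if a birth value is counted.
- Assumed: the change runs from the first to the last value. The article does not state the end points.
- Assumed: growth is linear, with independent residual SD σ and a between-infant SD of weekly growth rate equal to r × σ. The documents give neither σ nor r, so r is varied.

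**Share of values unused.** This is 1 − 2/K: 80% for K = 10, 67% for K = 6 and 50% for K = 4. It exceeds half once an infant has five or more values.

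**Variance, residual part only, K = 10.** For t = 0,…,9 the sum of squared deviations is Sxx = 82.5.
- Slope from all ten values: σ² / 82.5 = 0.0121 σ².
- Slope from first and last: 2σ² / 9² = 2σ² / 81 = 0.0247 σ².
- Ratio of the first to the second: 0.49.

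**Variance with between-infant differences in growth.** Scale the slope to the same interval of K − 1 weeks:
- Var(change) = (K − 1)² r²σ² + 2σ²
- Var(model slope × (K − 1)) = (K − 1)² r²σ² + (K − 1)² σ² / Sxx

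For K = 10 the ratio is (81r² + 2) / (81r² + 81/82.5), that is (81r² + 2) / (81r² + 0.982):

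| r | change / model slope |
|---|---|
| 0 | 2 / 0.982 = 2.04 |
| 0.1 | 2.81 / 1.792 = 1.57 |
| 0.5 | 22.25 / 21.232 = 1.05 |
| 1.0 | 83 / 81.982 = 1.01 |

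With fewer weekly values the range narrows: for r from 0 to 1 it is 1.40 to 1.02 for K = 6 and 1.11 to 1.02 for K = 4.

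So the gain runs from about 1% to roughly a halving of the variance. These figures are for infants with all K values and do not count infants who have no change score at all.

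**When the last value falls due.** Day 63 is nine weeks after birth, and 32 − 9 = 23. For any infant born after 23 weeks it therefore lies beyond 32 weeks' corrected age; an infant born at 29 weeks would be at 38 weeks. The Data collection section adds collection at discharge, so later values are foreseen, but some infants may leave before the last weekly measurement. A mixed model keeps their earlier values.

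**The case against.** The strongest reply is that nothing here is an error. A t-test or rank-sum test on a change score is a valid comparison in a randomised trial, and the article may add a supplementary model for one measure without contradicting itself. Which secondary outcomes get such a model is often left to an analysis plan. The first part stands: this is an improvement, not a correction of an invalid test. The last part carries less weight, because the article does not stay silent. It says which outcomes are longitudinal, and that list does not match its own schedule.

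Stronger readings are tempting, but the documents do not support them:

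- **That the three growth outcomes could not be compared with each other.** The model is introduced with the word *also*, so weight keeps the simple test too and all three measures share that analysis.
- **That length suffers most because it is measured with the largest error.** No section says anything about measurement error.
- **That the plan fixes a first-to-last change.** It says only that change is the outcome. The Data collection section mentions assessment at 32 weeks' corrected age and at discharge.
- **That unused values mean a large loss of precision.** The table shows that the loss may be close to nil.
- **That the model should replace the simple test.** With about 25% mortality, many infants without an end value will have died. A model fitted to all weekly values implicitly projects growth beyond death, so making it the sole analysis is debatable.

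**Conclusion.** The point holds as a minor inconsistency in the analysis of secondary outcomes. Length and head circumference are scheduled exactly as weight is, but as written they are denied the longitudinal analysis that weight receives.

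The size depends on how much true growth rates differ between infants, which the documents do not report. The variance ratio lies between about 2.04 and 1.01 for r between 0 and 1, given ten complete values, linear growth and a first-to-last change. The case for acting does not rest on the upper end of that range. It also rests on keeping infants who have some weekly values but no final one, under a missing-at-random assumption. Neither the primary analysis nor the sample size is touched.

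**What to change.** In the Statistical analysis section, extend the sentence on mixed-effect models so that it names weight, length and head circumference and the z-scores of all three, with the same model for each and all weekly values used. Keep the t-test or rank-sum comparison of the change scores alongside it. If length and head circumference are left out on purpose, give the reason.

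The cost is one sentence and a little more analysis work. The data are already to be collected and the type of model is already planned. When results are reported, state that the model assumes data missing at random and does not resolve truncation by death.

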## Discussion

Human milk provides the optimal nutrition as well as all the protective immune and developmental components needed for healthy infant development. The benefits of feeding preterm infants human milk are well-documented [27] and include decreased incidences of NEC, late-onset sepsis, feeding intolerance [6, 28], and BPD [27]. Our fresh milk study will evaluate the impact of feeding infants born at < 30 weeks’ gestation with fresh milk, within 4 h of its expression, on NEC ≥ stage 2 and on secondary outcomes, including sepsis, ROP, and BPD.

Human milk has many nutrients and bioactive factors that are beneficial to both term and preterm infants. Carbohydrates, particularly human milk oligosaccharides (HMO), are important for protection against infection, particularly NEC [29]. Furthermore, a multitude of proteins are present in human milk that form its essential nutrition and also play contributory roles in infant immune protection as well as the development of the immune system and the gut [30, 31]. Lipids come in many different forms and provide a major source of energy found in human milk [32]. Fatty acids, a type of lipid, are important for brain development [33] and can inactivate pathogens *in vitro* [34]. Finally, other bioactive components, including miRNAs [35, 36], stem cells, and microbes [37, 38], are present in human milk and are involved in immune response to infection and various aspects of development [37, 39–41].

Currently, the standard NICU procedure for fresh milk expressed by mothers of preterm infants is to freeze it and sometimes pasteurize it, depending on where the mother expressed it, before feeding. However, many components of human milk change with freezing, pasteurizing, and subsequent reheating. While carbohydrates remain relatively intact [42], bioactive proteins, lipids, and energy content are reduced after these steps of milk processing [﻿11﻿, ﻿43, 44]. In addition, following freezing, human milk shows lipid peroxide formation [45, 46]. Finally, no immune cell or stem cell activity is present following pasteurization or freezing or heating [﻿43﻿, 47].

*Cytomegalic virus* infection acquired from fresh human milk has been discussed as a potential safety concern in preterm infants [48]. However, the issue is controversial, and guidelines vary [49]. Some guidelines recommend that preterm infants are fed pasteurized mother’s own milk because of the potential risk of contamination by CMV. However, this may be unnecessary considering that if a mother is CMV positive, the infant already will have been exposed to CMV *in utero*. We will address this concern in our study by requiring every neonate admitted to the NICU to be tested for CMV and pasteurizing infected milk before use.

Oxidative stress is a major problem for ill infants and for preterm infants in particular; therefore, energy intake and antioxidant defense are crucial for preterm infants’ wellbeing [﻿45﻿]. Very preterm infants have diminished antioxidant capacity and are frequently exposed to oxidative stress from multiple sources such as infection, oxygen therapy, and mechanical ventilation. Furthermore, excess oxygen can secondarily lead to retinopathy of prematurity or chronic lung disease in preterm infants [﻿45﻿]. NEC, intraventricular/periventricular hemorrhage, and retinopathy of prematurity are all thought to be consequences of the imbalance between antioxidant capacity and oxidative stress [50]. Previous studies reported that human milk has important and essential antioxidant components, which may prevent and protect against diseases in infancy [45]. Human milk feeding remains an essential tool to help in the protection against free radicals, oxygen reactive species and oxidative stress, with fresh human milk having been reported to have the highest antioxidant activity [﻿45].

Our study will have some limitations. One limitation is a potential drop-out rate of 10% of enrolled families (based on our pilot study data) [﻿19﻿] due to factors such as time constraints. To minimize the potential bias from families leaving the study, we will use intention-to-treat analysis. If applicable, we will also conduct regression adjusted for propensity score estimated based on the infant and NICU characteristics available. Last, in China, approximately 17% of infants born preterm per year are discharged against medical advice and die at home. These infants will be included in our intention-to-treat analysis. To address this concern, we will perform a subgroup analysis of the primary outcome that only includes infants who were actively treated.

This study will be the first large, multicenter, prospective RCT to associate neonatal outcomes when feeding fresh human milk to preterm infants < 30 weeks’ gestation. Importantly, the results will determine the efficacy of fresh mother’s own milk to improve neonatal outcomes. The data of the study will be of significant interest to neonatal medical centers around the world, particularly because of the potential for fresh human milk to be a cost-effective way to improve and potentially optimize preterm infant care and outcomes.

